### 7-2 Secondary objectives

- To assess the morbidity of prophylactic radical fimbriectomy
- To determine the proportion of occult lesions on the radical fragmentectomy specimen (in situ and invasive cancer in the tube or adjoining ovary fragment)
- To assess the incidence of breast cancers or recurrence of breast cancers after fimbriectomy
- To determine the incidence of secondary oophorectomies and their morbidity
- To determine the incidence of benign histological abnormalities on radical Fimbriectomy specimens
- To assess patient satisfaction at a distance from radical Fimbriectomy

## 8 STUDY DESIGN

### 8-1 Methodology

This is a phase II, multicenter, non-drug, interventional biomedical study that assesses the feasibility of radical fimbriectomy in young women at hereditary risk of ovarian cancer.

### 8-2 Inclusion criteria

These are women in whom preventive adnexectomy is usually recommended.

#### ***All criteria are required for inclusion:***

- Women over 35 years of age
- After completion of the pregnancy
- BRCA 1 or 2 mutation, or family breast/ovarian documented by genealogy
- Not ready for bilateral adnexectomy (procedure that will always be routinely offered 1st)
- Involvement or not of breast cancer
- Affiliated with a social security plan

- Informed consent and signed by the patient prior to implementation of any study-specific procedures

### 8-3 Non-inclusion criteria

**Only one criterion is sufficient for non-inclusion:**

- Postmenopausal female defined as follows:
  - Bilateral oophorectomy
  - Not hysterectomized and amenorrheic for more than 12 months and/or FSH >20 IU/L, collapsed estradiol and progesterone, excluding chemo-induced amenorrhea
  - History of hysterectomy and FSH >20 IU/L
- Pregnant or breastfeeding woman
- Woman under temporary guardianship or guardianship

### 8-4 Early withdrawal criteria

- Discovery of invasive cancer or serous intraepithelial carcinomatous tubal lesion (or STIC for *Serous Tubal Intraepithelial Carcinoma*) on the fimbriectomy specimen

### 8-5 Study withdrawal criteria

Patients will be followed until menopause (no periods for more than 1 year).

The criteria for withdrawal from the study are:

- Post-fimbriectomy oophorectomy (patients will be followed 1 month post-procedure for complications)
- Patient decision
- Patient lost to follow-up
- Patient death

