## 6 INTRODUCTION AND STUDY RATIONALE

The identification, by linkage analysis in 1990 and then successive cloning of BRCA1 and BRCA2 genes in 1994 and 1995 disrupted the management of hereditary forms of breast and ovarian cancers. The molecular analysis of both genes now allows identification of a population of women at major risk of these cancers. More than 20,000 consultations and more than 9,000 tests for deleterious BRCA1/2 mutations were performed in France in 2009. Since 2003, the oncogenetic scheme has identified 8,488 people with a BRCA mutation [2009 INCa (*Institut national du Cancer* [National Institute of Cancer]) oncogenetic activity summary].

However, the cancer process remains multifactorial and penetrances are therefore highly variable. The cumulative lifetime risks are around 60 to 90% for breast cancers. For ovarian cancers, these risks are around 40% for BRCA1 and 20% for BRCA2. The mean age of onset is also later for BRCA2. The probability of these cancers occurring before the age of 50 is 5%-10% for BRCA1 and 1%-5% for BRCA2 [Chen 2007; Robson 2007]. The risks vary depending on the number of cases and age of occurrence in families [Metcalf 2010]. The baseline test is usually performed in an affected person to optimize these tests, which remain complex and expensive with waiting times for results of several months. The predictive test in asymptomatic patients leads to the identification of major breast and ovarian cancer risks and without known equivalent. For breast cancer risk, the majority of women choose specific screening (by MRI) given the physical and psychological consequences of bilateral mastectomy. The situation is different for pelvic risk, as we do not have an effective screening method but a less unacceptable preventive surgical solution than preventive breast surgery, especially in postmenopausal women. The seriousness of ovarian cancers, well known by clinicians as well as women who have had a case in the family, means that most mutated women will opt for preventive adnexal surgery, with or without hysterectomy. It is increasingly clear that adnexal preventive surgery provides the best risk-benefit in this situation with a reduction in both pelvic and breast cancer risk [Domchek 2010].

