## **6-2 Potential disadvantages of radical fimbriectomy [Greene 2010]**

- The rate of pelvic tumors that develop from the tube is not precisely known, and the benefit for these women will obviously be proportional.
- The idea is to perform castration afterward, closer to the natural age of menopause, and this will require a second pelvic procedure. Some women may not want to consider this second surgery, in the hope of a sufficiently reduced risk by removing the tube.
- The potential drawback that seems most important to us is the lack of reduction in breast cancer risk through ovarian suppression. Castration is generally known to reduce the risk of breast cancer, particularly tumors with steroid receptors. It is more than likely that this risk reduction is through ovarian hormone suppression. The studies confirm this risk reduction for women who have a BRCA1 and BRCA2 mutation [Rebbeck 2009]. However, it should be noted that in prospective studies this reduction in breast cancer risk is greater for BRCA2 mutations than BRCA1, which is not unexpected given the large proportion of tumors without BRCA1 receptors. However, the absence of a receptor may not necessarily reflect complete independence of the tumor from sex hormones. It should also be noted that these studies are observational and subject to risks of bias that are not always easy to identify or correct; therefore, the estimate of breast cancer risk reduction is only approximate [Heermskerk 2010]. One can also argue about the possibility of replacement therapy after castration; however, this treatment is contraindicated in breast cancer and some studies show that this treatment may not be as

effective as natural hormonal impregnation [Rebbeck 2009]. A substantial proportion of women who will be enrolled will likely have a history of BRCA1-related HR- breast cancer and the influence of castration on contralateral cancer risk is not really documented [Domchek 2010].

All of these arguments justify a prospective study of bilateral radical fimbriectomy that may help to better understand the risk-benefit ratio in this complex and very personal choice, but also to better understand the natural history of high-grade pelvic tumors that are obviously not just the prerogative of BRCA 1/2 mutations.

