### ***8-7-4 Incidence of secondary oophorectomy and their morbidity***

Their morbidity is also theoretical and very low. It involves possible gastrointestinal or ureteral injury related to the release of adhesions between the remaining ovaries and these structures as well as bleeding from the adnexal pedicle. The greatest risk is actually the development of ovarian cysts on the remaining ovaries, as the theoretical age of menopause approaches. However, this risk is not greater than that of the general population. It is the significance of these cysts in this particular context that should contribute to whether or not specific surgery is indicated. Complications related to secondary oophorectomy will be assessed up to one month post-procedure according to NCI-CTCAE v4.0.

The cumulative incidence of secondary oophorectomy is defined as the time from the date of the fimbriectomy to the date of the oophorectomy, with death without oophorectomy considered a competitive event. Patients alive without pelvic cancer or oophorectomy based on most recent information are censored at this time. The timing of the oophorectomy will also be described: prior to menopause, within 6 months of menopause onset, more than 6 months after menopause.

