### ***8-7-5 Postoperative complications***

Morbidity will be assessed:

- up to 30 days post-procedure according to the Clavien-Dindo classification [2009]
- and beyond this time (until confirmation of menopause for patients who have not had a secondary oophorectomy, or up to one month after secondary oophorectomy) according to the NCI-CTCAE v4.0 grading scale.

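### Section 8-5 ends follow-up on a menopause definition that conflicts with section 8-3, and cuts short an oophorectomy class planned in section 8-7-4

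*Protocol*

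**What the plan says.** Protocol section 8-5 fixes the end of observation: "Patients will be followed until menopause (no periods for more than 1 year". The parenthesis is the only definition given there.

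Section 8-3 defines postmenopausal status for the purpose of non-inclusion, and does so separately by uterine status. For women with a uterus: "Not hysterectomized and amenorrheic for more than 12 months and/or FSH >20 IU/L, collapsed estradiol and progesterone, excluding chemo-induced amenorrhea". For women without one: "History of hysterectomy and FSH >20 IU/L". Section 8-2 admits women with or without a history of breast cancer ("Involvement or not of breast cancer").

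Section 8-7-4 plans to describe the timing of secondary oophorectomy in three classes: "prior to menopause, within 6 months of menopause onset, more than 6 months after menopause". Section 6-2 places this second operation in time: "The idea is to perform castration afterward, closer to the natural age of menopause".

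Section 8-7-5 collects late morbidity "until confirmation of menopause for patients who have not had a secondary oophorectomy", without saying how menopause is confirmed. Appendix 2, the letter to the outside gynecologist, also describes yearly monitoring that lasts until menopause.

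**The concern.** The protocol uses one test of menopause to let women in and another to let them out. The exit test has neither the hormone condition for hysterectomised women nor the exception for chemotherapy. Two kinds of women whom 8-3 treats as premenopausal can therefore meet the 8-5 rule: those without a uterus, who have no periods whatever their ovarian function, and those whose periods stopped for over a year because of chemotherapy. If sites apply 8-5 as written, these women leave while they still have functioning ovaries and are still at risk of the primary event and of secondary oophorectomy.

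The second problem is internal to the endpoint section. Two of the three timing classes in 8-7-4 lie after menopause, but 8-5 stops looking at about that time. A class that the protocol has promised to report would be largely or wholly empty because of the follow-up rule, and a reader could take that as a finding about what women chose.

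**Working it through.** **1. The protocol's own figure.** This point disputes no number. The one decision rule it bears on is in 8-8-1: 8 tumours among 120 women, three years after the last enrolment, should give a one-sided 90% lower limit above 3%. It reproduces: 8/120 = 6.67%, with an exact (Clopper-Pearson) lower limit of 3.92%. The rule is arithmetically sound and stays so.

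**2. The two definitions side by side.**
- *Hysterectomised, FSH at or below 20 IU/L.* Under 8-3 she is not postmenopausal and is eligible. Under 8-5 she has had no periods for over a year once a year has passed since the hysterectomy, which may already be so at enrolment. The definitions disagree.
- *Uterus present, over a year of chemotherapy-induced amenorrhoea.* Under 8-3 that amenorrhoea is set aside. Under 8-5 it counts. The definitions disagree.
- *Uterus present, natural amenorrhoea for over a year.* Both definitions call this menopause. They agree.

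Neither conflicting case is excluded by the entry criteria. Section 8-3 writes a separate limb for hysterectomy, and 8-2 admits women who have had breast cancer.

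**3. Whether another section repairs 8-5.** Section 8-7-5 speaks of confirming menopause but gives no method. Section 8-7-5-3 describes confirming induced menopause by absent periods together with a hormone panel, in the context of a surgical risk. Section 8-6-3 provides hormone tests in follow-up only when there is cycle disturbance or menopausal symptoms. None of these is tied to 8-5, and a hysterectomised woman without symptoms would trigger no test.

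**4. The window for oophorectomy timing.** Let month 0 be the last period. Section 8-5 closes observation at about month 12. Classes two and three of 8-7-4 are separated at 6 months after menopause.
- *Menopause dated at the last period.* Class two covers months 0 to 6 and is fully observed. Class three starts at month 6 and is seen for 12 − 6 = 6 months.
- *Menopause dated at the twelve-month point.* Observation after menopause is 12 − 12 = 0 months. Neither class two nor class three has a window.

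The protocol does not say which dating applies.

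**5. Effect on the endpoints.** In the competing-risks estimate, a woman who exits early is censored. This costs time at risk and precision, but is not in itself a bias. The 8-of-120 rule is a count over a fixed denominator, so early exits within three years can only lower the count. The size cannot be derived. For scale only, assume a true 3-year risk of 10% and let a fraction f stop at time t, with t between 1.0 and 1.5 years. With h = −ln(1 − 0.10)/3, the observed risk is (1 − f) × 0.10 + f × (1 − exp(−h·t)).
- f = 0: 12.0 expected tumours, and the probability of 8 or more is 92.2%.
- f = 10%: 11.21 to 11.42 expected, 88.2% to 89.4%.
- f = 20%: 10.43 to 10.83 expected, 82.8% to 85.8%.

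The values of f, t and the 10% are assumptions. They show direction and are not an estimate for this trial.

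**The case against.** The best defence is that menopause is the operative word in 8-5 and the parenthesis only a gloss. Menopause is not among the four listed withdrawal criteria, 8-3 already contains the fuller definition, and no sensible site would end follow-up of a hysterectomised woman on the day she enrols. Sites may well use the hormone panel. This limits the likely harm, but it asks sites to depart from the text of 8-5, and nothing tells them to do so in the same way. Yearly visits may also place the exit visit somewhat after month 12, so some later operations could be picked up. That is an accident of visit timing, not a planned window.

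Four stronger readings are tempting, and the documents do not support them.

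- *Most of the cancer risk is left out.* Section 6 says "For ovarian cancers, these risks are around 40% for BRCA1 and 20% for BRCA2" and puts 5-10% and 1-5% before age 50. The share after 50 is then 1 − 10/40 = 75% to 1 − 5/40 = 87.5% for BRCA1, and 1 − 5/20 = 75% to 1 − 1/20 = 95% for BRCA2. The arithmetic is right, but this is lifetime risk split at an age that the protocol does not equate with menopause, and it does not describe women after fimbriectomy. The trial studies a temporary step before removal of the ovaries and judges it at three years. The share is not a measure of error.
- *Chemotherapy-related exit is informative for both cancer endpoints.* A breast cancer arising on study is already the breast event at diagnosis, so later exit cannot censor it. For pelvic cancer, the documents offer no link between this amenorrhoea and risk.
- *Most second operations are missed.* No distribution of oophorectomy timing is given, and operations before menopause and, under one dating, for twelve months after the last period are recorded.
- *All women must be followed to the projected end in 2034.* Stopping near menopause is a choice of scope that fits the bridging purpose. The protocol need only keep its conclusions within it.

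**Conclusion.** The point holds as a contradiction between sections with a practical consequence. As written, 8-5 can end observation of women whom 8-3 regards as premenopausal, with lost time at risk for pelvic cancer and secondary oophorectomy. It also leaves the third timing class of 8-7-4 six months of planned observation, or none, depending on an unstated dating convention. The first part rests on a literal reading of 8-5 and on no other section overriding it. The number of women concerned is not known. The second part rests only on the wording of 8-5 and 8-7-4. No bias in the three-year estimate is shown, and the final decision rule is not made wrong. The conflict should be corrected, but it is a matter of consistency and scope and does not invalidate the design.

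**What to change.** - Reconcile 8-5 with 8-3 so that a single menopause definition governs the end of follow-up. State what information establishes it in hysterectomised women and after chemotherapy, and carry the same wording into 8-7-5 and Appendix 2. The choice of definition is a clinical one for the sponsor.
- Record the menopause date as a data item, and state whether onset is dated from the last period or from the twelve-month point.
- Then choose one of two courses. Either collect a brief status item after menopause (secondary oophorectomy, pelvic cancer) through the Appendix 2 letter, which already asks about pelvic cancer and further pelvic surgery. Or restate the third class in 8-7-4 to match what is observed, and limit conclusions on secondary oophorectomy and long-term pelvic cancer incidence to the period before confirmed menopause.

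The cost is a short amendment. The first course adds a small amount of data collection and possibly renewed information to patients, and since recruitment closed in October 2014, women who have already left may be hard to reach. The second course costs only wording and a narrower claim.

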### 8-6 Assessment Report

#### 8-6-1 Inclusion assessment

Written consent from the patient must be obtained prior to implementation of any study-specific procedures. Patients eligible for the trial must undergo a baseline assessment within 28 days before surgery. At the same time, the relevant history (risk factors, associated diseases) will be recorded.

| Type of Assessment                                                                                                 | Timeline - Comments                                                  |
|--------------------------------------------------------------------------------------------------------------------|----------------------------------------------------------------------|
| Information and collection of written consent                                                                      | To be obtained and signed by the patient and the investigator |
| Demographics
Relevant history (risk factors, associated diseases)
Last menstrual period date                 | Prior to enrollment
and within 28 days prior to surgery           |
| PHYSICAL EXAMINATION
Gynecological examination
Anesthetic evaluation of surgical non-contraindication |                                                                      |
| LABORATORY TESTS
- FSH, estradiol, inhibin B and anti-Müllerian hormone (ovarian reserve)
- CA-125    |                                                                      |
| - $\beta$ -HCG                                                                                                     | Before enrollment and within 7 days prior to surgery          |

### **8-6-2 Post-operative assessment**

| Type of Assessment                                                                                                                       | Timeline - Comments   |
|------------------------------------------------------------------------------------------------------------------------------------------|-----------------------|
| PHYSICAL EXAMINATION 

- Physical examination

- Postoperative Complications

 | 30 days after surgery |

### **8-6-3 Follow-up report**

The primary objective of radical fimbriectomy is to reduce the risk of serous pelvic carcinoma (ovarian or peritoneal) with a predominant tubal origin, while awaiting definitive castration.

Since a large portion of the ovaries is left in place, there is a residual risk of high-grade serous carcinoma that is probably very low but not zero. It could be due to the degeneration of STIC tissue left in place on the ovary (but which would also exist on the fimbriectomy specimen) or by the degeneration of inclusion cysts [Kurman, 2010]. Finally, the development of any other type 1 tumor can be observed from tissue included in these same cysts or a non-epithelial tumor, germ cell tumor, or sex cords that is not related to the BRCA gene abnormality.

Any abnormal abdominal or gynecological symptoms, whether there is a genetic background or not, should result in appropriate imaging being performed, possibly repeated or supplemented by surgery. The follow-up of these asymptomatic women at risk should also be considered.

Surveillance methods have proved ineffective at screening for high-grade serous carcinoma. However, they make more sense when it comes to detecting a type 1 tumor or a non-epithelial tumor that usually grows more slowly.

To date, the screening combining the annual CA-125 blood test followed-up according to its transvaginal ultrasound result, appears to be the combination that leads to the least "unnecessary" surgeries while detecting most early cancers, as shown in the largest randomized screening study conducted to date [Menon 2009].

For other women without lesions identified on the fimbriectomy specimens, we thus propose to base the pelvic monitoring procedures of these women on this protocol. This gynecological screening will be combined with breast disease screening.

If a test is abnormal, it is repeated. In case of persistent abnormality, further clinical assessment (MRI) or surgical follow-up will be discussed.

| Type of Assessment                                                                                               | Timeline - Comments                                                |
|------------------------------------------------------------------------------------------------------------------|--------------------------------------------------------------------|
| PHYSICAL EXAMINATION
Gynecological examination
Additional examination left to clinician discretion  | Once a year                                                        |
| LABORATORY TESTS
- FSH, estradiol, inhibin B and anti-Müllerian hormone (ovarian reserve)              | In case of menstrual disorders or menopausal symptoms              |
| - Annual CA-125                                                                                                  | Once a year                                                        |
| PARACLINICAL EXAMINATIONS
- Transvaginal and suprapubic ultrasound
- ± pelvic MRI if clinical signs | Pelvic ultrasound, if marker increase confirmed by a second sample |
| QUESTIONNAIRE
- Satisfaction questionnaire                                                             | Once during follow-up                                              |

The investigator must inform the non-hospital gynecologist of the patient's participation in the trial, and the need to investigate, at each consultation:

- any adverse event that may reasonably be related to surgery, such as menstrual disorders, hot flashes, vaginal dryness, etc., until the onset of menopause;
- any signs suggestive of pelvic cancer, breast cancer, or its recurrence;
- and any additional pelvic surgery procedure

A letter for non-hospital gynecologists is provided for this purpose (Appendix 2).

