| Duration of recruitment:              | 33 months (OCT2014)                                                                                                                                                                                                                                                                                                                                                                                                                                                                                                                                                                                                                                                                                                                                                                                                                                                                                                                                                                                                                                                                                                                                                                                                                                                                                                                                                                                                                                                                                                                                                                                                                                                                                                                                                                                                                                                                                                                                                                                                                                                                                                                                                                        |                     |         |                          |                     |               |                     |

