#### *8-7-5-3 Expected serious adverse event (expected SAE)*

An expected SAE is an event already mentioned in the literature data.

Perioperative morbidity from prophylactic laparoscopic adnexectomy is very low. The rates of intraoperative complications were reported at 1.3% and postoperative complications at 3.1% with a **conversion rate to laparotomy** of 0.8% in a series of 159 patients [Kenhuis 2010]. There is no theoretical reason why fimbriectomy has higher levels than this. Apart from the known risks of any laparoscopic procedure, the specific operative morbidity of radical fimbriectomy would be limited to the sole risk of **postoperative bleeding** of the remaining ovaries. An inspection of the ovarian cut section after deflation of the pneumoperitoneum over a few minutes and re-insufflation enables sealing with a few elective bipolar coagulations if necessary.

Later, the **risk of induced menopause** may theoretically be observed if the two sources of blood supply from the ovary (adnexal and infundibulopelvic pedicle) were altered by the procedure. This risk is naturally increased in case of a single adnexa. If menopause is confirmed by the absence of periods

and a hormone panel (LH and FSH plasma estradiol), the additional oophorectomy could be discussed with the patient sooner.

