Early postoperative morbidity (assessed by Clavien-Dindo scale within 30 days post-operatively) and late postoperative morbidity (occurring in a period of more than 30 days and assessed by NCI-CTCAE) will be described by type of adverse event, grade and relationship to the fimbriectomy or secondary oophorectomy. The type of adverse event (AE) will be described by SOC (System Organ Class) and PTname (Preferred Term) of the medDRA medical dictionary. The maximum grades observed by type of AE will be described in tabular form: number and frequency. Serious adverse events (SAE) will be described.

Each item of the satisfaction questionnaire will be described by its median, extreme values, mean and standard deviation.

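### The planned late-morbidity output has no age or time axis and no criterion to tell early or possibly induced menopause from natural menopause

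*Protocol*

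**What the plan says.** **Who enters and how long they are followed.** The first inclusion criterion in section 8-2 is "Women over 35 years of age", with no upper limit. The first non-inclusion criterion in section 8-3 begins "Postmenopausal female defined as follows", so natural menopause still lies ahead for every participant. Section 8-5 states "Patients will be followed until menopause (no periods for more than 1 year", with earlier exit for oophorectomy, the patient's decision, loss to follow-up or death.

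**What is collected.** After day 30, section 8-7-5 records morbidity on the NCI-CTCAE scale "until confirmation of menopause for patients who have not had a secondary oophorectomy", or to one month after that operation. Section 8-6-3 has the investigator ask the non-hospital gynecologist to look, at each consultation, for "any adverse event that may reasonably be related to surgery, such as menstrual disorders, hot flashes, vaginal dryness, etc., until the onset of menopause". The letter in Appendix 2 repeats the list.

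**What is named as a risk.** Section 8-7-5-3 says that induced menopause "may theoretically be observed if the two sources of blood supply from the ovary" were both affected by the procedure. Appendix 6 lists menopause, without qualifier, among the expected postoperative serious events.

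**What is reported.** Section 8-8-2 describes late morbidity by event type, grade and relationship to either operation, and adds: "The maximum grades observed by type of AE will be described in tabular form: number and frequency". Serious events are also described. Apart from the split at 30 days, no time or age axis is given.

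**The concern.** Morbidity of fimbriectomy is the first secondary objective (section 7-2). Part of the case for the operation is that the ovary left behind keeps enough hormonal activity to spare women an early, abrupt menopause (section 6-1). Whether that holds is the late safety question that matters most to a woman choosing between this operation and adnexectomy.

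The collection window runs through the ordinary menopausal transition, and its usual symptoms are suggested in advance as possibly surgical. Nothing in the protocol says by age, by time since surgery or by hormone level when menopause counts as early or possibly induced. A hot flash at 39, one year after surgery, and a hot flash at 50, twelve years after surgery, enter the same cell of the table. Only the investigator's judgement of relationship separates them, and that judgement has no stated criterion. The planned summary could look much the same whether or not the operation brought menopause forward in some women.

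**Working it through.** The protocol gives no rate, sample size or power for late morbidity or menopause, so it has no figure to reproduce. The check has four steps. The dates and the 120 patients come from the protocol. The distribution of natural menopause age, the symptom frequencies, the share keeping their ovaries and the size of a surgical effect are assumptions.

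**1. Length of follow-up.** Recruitment ran from JAN2012 to OCT2014 and the projected end is AUG2034 (synopsis).
- Last woman enrolled: OCT2014 to AUG2034 = 19.8 years.
- First woman enrolled: JAN2012 to AUG2034 = 22.6 years.
- Youngest possible age at study end: just over 35 + 19.8, about 55.

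**2. Share reaching natural menopause before study end, absent oophorectomy or death.** Assume a normal distribution of menopause age with survivor function S. For a woman aged a and premenopausal at surgery, the share is 1 − S(a + 19.8)/S(a).

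| Age at surgery | Lowest (mean 52, SD 5) | Mean 51, SD 4 | Highest (mean 49, SD 3) |
|---|---|---|---|
| 36 | 78% | 89% | 99% |
| 40 | 94% | 99% | 100% |
| 45 | 99% | 100% | 100% |

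**3. Women in the late table with menopausal symptoms.**
- Natural course = 120 × share reaching menopause with ovaries in place × share with recorded symptoms. Low: 120 × 0.4 × 0.3 = 14.4. High: 120 × 1.0 × 0.8 = 96.
- Surgical effect = 120 × share affected. Low: 120 × 0.02 = 2.4. High: 120 × 0.10 = 12.
- Surgical share of symptomatic women = surgical / (natural + surgical). Lowest: 2.4 / (96 + 2.4) = 2%. Highest: 12 / (14.4 + 12) = 45%.
- Over the grid (ovaries kept 0.4, 0.7, 1.0; symptoms 0.3, 0.5, 0.8; effect 2%, 5%, 10%), the surgical share is below one third in 25 of 27 combinations and below one half in all.

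**4. What an age axis would show.** Take a woman operated on at 36, menopause age with mean 50 or 51 and SD 4, and an induced share of 5%, all occurring before 45. With p the natural probability, the probability with surgery is 0.95p + 0.05, a rise of 0.05(1 − p).
- Menopause by study end: p = Φ((36 + 19.8 − 50)/4) = Φ(1.45) = 0.926, or Φ(1.20) = 0.885 with mean 51. The rise is 0.05 × 0.074 = 0.4 points, or 0.05 × 0.115 = 0.6 points.
- Menopause before 45: p = Φ(−1.25) = 0.106, or Φ(−1.50) = 0.067. It becomes 0.95 × 0.106 + 0.05 = 0.151, or 0.95 × 0.067 + 0.05 = 0.114. The rise is about 4.5 to 4.7 points.

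The same effect is almost invisible in an end-of-study frequency and visible on an age scale. The background on that scale also depends on the assumptions. For 120 women entering at 38, with mean 49-52 and SD 3-5, natural menopause before 40 is expected in about 0 to 3 and before 45 in about 1 to 24.

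**The case against.** Several objections are sound and limit the point.

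- **The list in section 8-6-3 does not classify anything.** It tells an outside gynecologist what to look for. Section 8-7-5-1 requires onset date and relationship to surgery for each event, and section 8-8-2 reports by relationship. A reader might infer that menopausal symptoms are counted automatically as surgical. The text does not say so. It suggests the link in advance and leaves the judgement open.
- **The data exist.** A reader might also infer that induced menopause cannot be seen at all. But last menstrual period and ovarian-reserve hormones are taken at baseline (section 8-6-1), symptoms trigger further hormone tests (section 8-6-3), events carry onset dates, and menopause has to be established to end follow-up and to time oophorectomy against it (section 8-7-4). A case judged serious and related also has its own reporting route without time limit (section 8-7-5-6). What is missing is an output that uses this information.
- **Not every woman reaches natural menopause under observation.** The operation is meant as a bridge to later removal of the ovaries, which ends participation. A table heading towards 100% is therefore not supported. Reaching menopause is also not the same as a recorded adverse event.
- **Early menopause has other causes.** Section 6-2 expects many women with previous breast cancer, and section 8-3 recognises chemotherapy-induced amenorrhea. Counting every menopause before some cut-off as surgical could mislabel these women.
- **Table layout can wait for the statistical analysis plan.** That is true of age bands. But the protocol itself fixes the collection window and the summary for a complication it names, and it makes neither age at menopause nor time to menopause an endpoint.

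What remains is a gap in the endpoint list and in the planned output. It does not show that the morbidity objective fails.

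**Conclusion.** The point holds in a limited form. As written, the late-morbidity output cannot show whether the operation preserved ovarian function. It pools the menopausal transition over up to about 20 years, has no age or time axis, and separates surgical from natural cases only by a judgement without a stated criterion.

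On the assumed inputs, natural menopause accounts for more than half of the women with menopausal symptoms in every combination tried, and for more than two thirds in 25 of 27. These shares apply before any split by relationship. They depend on assumptions about menopause age, symptom reporting, size of surgical effect and share keeping their ovaries, none of which the protocol gives.

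The omission stands out because section 8-8-2 already uses competing-risk cumulative incidence for pelvic cancer, breast cancer and secondary oophorectomy, and estimates both cancers by age reached as well. Menopause, the late risk that the protocol itself names, gets no such analysis.

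**What to change.** - In sections 8-7 and 8-8-2, add menopause as a descriptive endpoint. Estimate its cumulative incidence by attained age and by time since fimbriectomy, with secondary oophorectomy and death as competing events.
- Describe it by baseline age, baseline AMH and FSH, and prior chemotherapy.
- Keep every adverse event in the safety table, but show menopause and menopausal-symptom events as a separate block with age at onset and time since surgery.

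**Cost.** One further descriptive analysis and a few lines of text, with no change to visits or care. Most inputs are already collected. Before the text is changed, the sponsor should confirm that the case report form holds the date of menopause and prior chemotherapy, because the protocol implies both but lists neither as a named item.

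**Limit.** Without a comparator, the curves describe when menopause occurs after this operation. They do not prove that surgery caused it.
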